## Abstract

**Background:**

In European countries, including Switzerland, cannabis is the most commonly used illicit drug. Offering a Web-based self-help tool could potentially reach users who otherwise would not seek traditional help. However, such Web-based self-help tools often suffer from low adherence.

**Objective:**

Through adherence-focused guidance enhancements, the aim of this study was to increase adherence in cannabis users entering a Web-based self-help tool to reduce their cannabis use and, in this way, augment its effectiveness.

**Methods:**

This paper presents the protocol for a three-arm randomized controlled trial (RCT) to compare the effectiveness of (1) an adherence-focused, guidance-enhanced, Web-based self-help intervention with social presence; (2) an adherence-focused, guidance-enhanced, Web-based self-help intervention without social presence; and (3) a treatment-as-usual at reducing cannabis use in problematic users. The two active interventions, each spanning 6 weeks, consist of modules designed to reduce cannabis use and attenuate common mental disorder (CMD) symptoms, including depression, anxiety, and stress-related disorder symptoms based on the approaches of motivational interviewing and cognitive behavioral therapy. With a target sample size of 528, data will be collected at baseline, 6 weeks, and 3 months after baseline. The primary outcome measurement will be the number of days of cannabis use on the preceding 7 days. Secondary outcomes will include the quantity of cannabis used in standardized cannabis joints, the severity of cannabis dependence, changes in CMD symptoms, and adherence to the program. Data analysis will follow the intention-to-treat principle and employ (generalized) linear mixed models.

**Results:**

The project commenced in August 2016; recruitment is anticipated to end by December 2018. First results are expected to be submitted for publication in summer 2019.

**Conclusions:**

This study will provide detailed insights on if and how the effectiveness of a Web-based self-help intervention aiming to reduce cannabis use in frequent cannabis users can be improved by theory-driven, adherence-focused guidance enhancement.

**Trial Registration:**

International Standard Randomized Controlled Trial Number Registry: ISRCTN11086185; http://www.isrctn.com/ISRCTN11086185 (Archived by WebCite at http://www.webcitation.org/6wspbuQ1M)

## Introduction

### Epidemiology

According to the European Drug Report 2016 [1], approximately 13% of Europeans in the age range of 15 and 34 years have used cannabis in the last year; it is by far the most commonly used illicit drug. Translated into absolute numbers, there are approximately 16.6 million Europeans who use cannabis, with roughly one percent of European adults estimated to use cannabis daily [1]. Within Europe, Switzerland ranks third in the national prevalence of cannabis use: the lifetime prevalence rate of cannabis use is 27.9% (men 32.8%, women 23.2%), whereas the 6-month prevalence rate is 5.4% (men 7.6%, women 3.3%). The highest prevalence is found in the age group between 15 and 24 years. Within this group, the 6-month prevalence rate is 14.4%, with almost one-fifth of users using cannabis daily [2].

Even though these numbers are high, only a minority of cannabis users seem to develop cannabis dependence; in general population surveys, the risk of becoming dependent on cannabis appears to be between 10% and 11% among all cannabis users [3,4]. However, within the subgroup of cannabis users who started using cannabis in early life, the risks of cannabis dependence [5] and cannabis use problems [6] are much higher.

Although cannabis dependence has not been shown to increase mortality in the general population, its impact on the global burden of disease should not be understated. Expressed in disability-adjusted life years (DALYs), which is the sum of years of life lost because of premature mortality and years lived with disability, it has been estimated that, in 2010, cannabis dependence accounted globally for approximately two million DALYs [7].

Furthermore, poorer mental and physical health, lower educational achievement, and decreased cognitive functioning are all commonly seen in daily cannabis users [8]. Numerous studies also point to the associations between a broad range of primary mental illnesses and frequent cannabis use, highlighting the potential for detrimental effects of co-occurring mental health disorders on treatment in problematic cannabis users [9].

Patients who seek treatment for their cannabis use disorder at Swiss outpatient addiction treatment centers are mainly young males in the age range of 15 and 24 years [10]. Data from the monitoring system for addiction counseling and addiction treatment in Switzerland suggest a linear increase in new patients for whom cannabis is the main problem substance from 2004 (8.8%) to 2014 (46.7%) [11], a trend that has also been observed in other European countries [1]. However, it is clear that even though the number of treatment seekers has steadily increased, they still represent the minority of problematic cannabis users (eg, scoring 8 or higher on the Cannabis Use Disorder Identification Test) [12] who could potentially profit from treatment, among whom approximately half develop cannabis dependence [5], and many suffer from comorbid mental health problems [9].

### Accessibility and Reachability

There are various possible reasons why the percentage of problematic cannabis users who seek treatment is still so low. First among them are problems with accessibility: as addiction treatment centers are rare, low accessibility force potential treatment seekers, especially those living in more rural areas, to travel considerable distances. This increase in time required for travel is especially a hindrance, given that most addiction counseling centers operate during normal office hours, rendering attendance for potential treatment seekers almost impossible if they have a job that requires them to work during these hours [10,13]. The second reason pertains to the issue of stigmatization, with the fear of being stigmatized as a drug addict likely preventing many problematic cannabis users from seeking face-to-face treatment. As older individuals generally have greater social responsibilities, it is quite possible that the levels of fear increase as the age of users increase. Consistent with this assumption, users of Web-based self-help tools for the reduction of problematic cannabis use appear to be older and use more cannabis than those who seek help at outpatient addiction treatment centers [10].

Issues relating to self-efficacy also can be problematic, as some users have the desire to quit or reduce their cannabis consumption on their own [14]. Finally, many cannabis users lack insight into the various problems potentially caused by their cannabis use. For example, although many users are aware of some side effects of problematic cannabis use, such as mild depressive symptoms, the physical risks associated with the combustion and inhalation of smoke are often overlooked. These risks include heart disease, lung cancer, and chronic obstructive pulmonary disease [15,16]. Frequent users are more prone to disregard these risks than occasional users, but increased awareness could be advantageous for all, as it has been shown that the more users know about the possible physical risks of problematic cannabis use, the greater their intention to quit or at least reduce their cannabis use is [15,16].

Web-based self-help programs to reduce problematic substance use, such as—in the case of cannabis—CANreduce, could be a great asset in reaching those groups within the general population who would otherwise not seek treatment. Such programs facilitate access by being available around the clock and easily reachable from any home that has a computer and an Internet connection. Nowadays, many Web-based self-help programs also work on mobile devices, making almost any situation a potential treatment session. Apart from this huge improvement in accessibility relative to regular bricks and mortar treatment centers, Web-based programs also solve the fear of stigmatization issue. Allowing for anonymity, as well as enabling self-efficacy, it is often an ideal solution for at least a subgroup of users. Apart from all this, these noninvasive tools are low-cost and, depending on how they are set up (eg, whether or not they have counselors on standby for chat sessions), require little maintenance effort, lowering the costs once developed to just Web server space, domain name registration, minimal administrative support, and the effort needed to regularly update techniques and design. Naturally, this is of great interest amid the current environment of constantly increasing health care costs, as is the case in Switzerland and other industrialized countries [17].

### Previous Studies and Implications

However, all the aforementioned positive characteristics of such Web-based self-help programs only hold true if they actually are effective in their goal of reducing problematic cannabis consumption. This has indeed been consistently shown for programs aiming to reduce problematic alcohol use [18,19] and also—albeit to a lesser extent and not as consistently—for programs aiming for tobacco smoking cessation [20,21]. The Web-based approach for the most commonly used illicit drug, cannabis, has not been studied as thoroughly. To our knowledge, only two Web-based self-help programs to reduce problematic cannabis consumption have been tested for their effectiveness in appropriate RCTs in adults [10,22].

“Reduce Your Use: How to Break the Cannabis Habit” is an Australian self-help intervention that is fully automated and consists of six modules which are—similar to CANreduce—based on cognitive behavioral therapy (CBT), motivational interviewing (MI), and behavioral self-management. In an RCT, this intervention was shown to be more effective at reducing the frequency and quantity of cannabis consumption than a psychoeducational control condition. Regarding adherence to the 6-week program, two-thirds of the initial participants completed the intervention [22].

In addition, a previous version of CANreduce has been investigated with the objective of determining whether a Web-based self-help tool for reducing problematic cannabis consumption would be more effective if individualized chat sessions with a professional coach are offered [13]. Although the study found that participants who were in the group with the opportunity for individual chat sessions reduced their frequency of cannabis use more than those who only worked with the self-help tool, the effect was also identified among those in a chat sessions group who did not actually make use of the chat offer (ie, who did not reply to chat-based consultation appointments offered by professional chat counselors). Thus, it appears that even just the option of having chat appointments reduced cannabis consumption [10]. With only a quarter of participants who were given the option of scheduling a chat session actually taking advantage of the offer, the question was raised as to whether the same effect could be recreated by simpler means, eliminating the need for professional counselors on constant standby.

With CANreduce 2.0, we try to address this problem by implementing adherence-focused guidance, which has already been documented to be effective at increasing adherence to Web-based self-help relative to Web-based self-help alone [23,24]. The concept of adherence-focused guidance is primarily based on the supportive-accountability model of guidance in Web-based interventions [25] that asserts that unguided self-help programs are often less effective than those that are guided [26]. However, Mohr’s model for adherence to electronic health (eHealth) interventions encompasses further factors, which we additionally attempt to address, to strengthen the concepts of accountability and legitimacy with the assumption of thereby increasing the effectiveness of the support in terms of adherence. Specifically, we emphasize the *social presence* factor and those factors that increase program legitimacy as defined by Mohr’s model [25].

Furthermore, almost two-thirds of CANreduce participants in the former study screened positive for clinically relevant depression symptoms at baseline [10]. Moreover, even if partakers of intervention programs do not exhibit depressive symptoms at baseline, it is possible that such symptoms could emerge as they decrease their drug use. Comorbidity of depressive symptoms and substance use and its hindrance on positive treatment outcomes has been demonstrated several times before [27]. Furthermore, targeting a reduction in depressive symptoms in patients simultaneously could possibly increase adherence to the program. Therefore, the new version of CANreduce also aims to specifically target issues that potentially help to ameliorate depression and other common mental disorder (CMD) symptoms such as those associated with anxiety and stress-related disorder using CBT [27] and teaching social problem-solving skills [28]. Moreover, we incorporated aspects within modules targeting excessive rumination and worry, as well as difficulties with relaxing.

### Study Aims

The study presented in this protocol seeks to investigate and compare the effectiveness of Web-based self-help interventions at reducing cannabis use in problematic users, while taking into account the most frequently co-occurring mental health symptoms. Moreover, it examines whether adherence to the program can be optimized by emphasizing the social presence factor of adherence-focused guidance, which would only marginally increase costs versus guidance that is less personal.

## Methods

### Study Design

The Web-based self-help program CANreduce will be evaluated within a three-arm RCT, comparing the effectiveness of an adherence-focused, guidance-enhanced, Web-based self-help intervention with a social presence; an adherence-focused, guidance-enhanced, Web-based self-help intervention without a social presence; and treatment-as-usual (TAU) at reducing cannabis use in problematic users. The masking technique will be partially single-blinded—in that participants in either of the two active treatment groups will not know which version they work with. The two versions are neutrally described as two differently optimized variants to prevent participants from having a preference of one over the other possibly resulting in a disappointment when being allocated to the unwished version. However, subjects will know whether they have been assigned to TAU. Any blinding of research and study personnel is not warranted. After successful completion of the baseline assessment (t0), participants will be allocated to one of the three study conditions. Further assessments will take place both 6 weeks (t1) and 3 months (t2) after baseline (Figure 1). The trial has been registered with the ISRCTN registry and is traceable as ISRCTN11086185.

### Recruitment of Study Participants

Recruitment will take place from August 2016 to December 2018 to ensure that the target sample size of 528 participants has been included. Participants will be recruited through the CANreduce website itself [29], which is already established and has links to it on various Internet health portals. Additionally, advertisements will be placed in relevant Internet forums and newspapers (or Web-based versions thereof).

For compensation, all participants who complete 3 months of follow-up from the start of the program will be able to choose between an Web-based voucher worth 30 Euro or donating that amount to charity.

### Registration and Consent Procedure

Participants can register online and will need to provide only minimal personal data, including their email addresses, phone numbers (only to get in contact with if follow-up questionnaires are not filled out), and some basic demographical data (age, gender, and level of education).

Before registration, each participant will be informed online about the study, specifically provided information about the following:

Purpose, background, and an overview of the studyInclusion and exclusion criteria (Tables 1 and 2)The difference between the three treatment arms (but no details about how the two active treatment arms differ) and their one in three chance of being allocated to each one of these three armsFinancial aspects (no participation fee, compensation for participation)Potential risks of participation and when to contact their general practitioner or, alternatively, a professional they can select from a medical advisory and emergency list that will be accessible at all times merely by clicking on emergency iconThe inability of CANreduce to replace face-to-face therapy for problematic cannabis use or abuseThe voluntary nature of participation and their right to withdraw from the study at any time without consequences, except for the loss of further compensationConfidentiality and data protection (anonymity is ensured by not recording real names or postal addresses and by deleting email addresses and phone numbers before statistical analysis and data archiving)The approval given by the ethics committee of the Canton Zurich after the committee had reviewed the study

Informed consent will be accepted once participants have activated several check boxes restating important study points and have submitted their consent by clicking a submission button.

### Randomization and Trial Flow

Once participants have completed their baseline assessment, they will be randomized by a computer algorithm in a 1:1:1 ratio into one of three parallel groups, and this assignment will be registered automatically in the background database. 

**Figure 1 figure1:**
[figure not shown]
Trial flowchart.

**Table 1 table1:** Inclusion criteria and underlying rationale.

Inclusion criteria	Reasoning
Informed consent via the Web form	To ensure knowledge of procedures and the declaration of consent
Minimal age of 18 years	To ensure a minimum age of participation
Cannabis use at least once weekly over the last 30 days	To include participants with less than daily cannabis use, increase validity
At least once weekly Internet access and a valid email address	To ensure at least some access to the intervention
Good command of the German language	To ensure that participants will be able to understand the information provided

**Table 2 table2:** Exclusion criteria and underlying rationale.

Exclusion criteria	Reasoning
Participation in other psychosocial or pharmacological treatments for the reduction or cessation of cannabis use	To avoid confounding treatment effects
Current pharmacologically treated psychiatric disease or any history of psychosis, schizophrenia, bipolar type I disorder, or significant current suicidal or homicidal thoughts	To avoid having subjects with these problems enter the study

As participants assigned to TAU will immediately become aware of this, we expect that some might try to circumvent their assignment by registering another account, hoping to end up in a different group. If anyone attempts this, he or she nevertheless will be assigned to the original group when they try to register again on the same day based upon his or her Internet protocol address.

Participants will be introduced step by step into the corresponding study arm and, in the cases of study arms 1 and 2, be invited to participate in the program. Participants assigned to study arm 3 will be informed that they will be provided access to the Web-based self-help treatment after 3 months (with TAU until they are 3 months past their baseline assessment). Participants in study arms 1 and 2 will receive automated email notifications to log in and enter their cannabis consumption quantity and frequency into their consumption diary every week.

The two experimental interventions will each last 6 weeks. Follow-up assessments will be 6 weeks and 3 months after the start of the program. As such, there will be a baseline (pretreatment) assessment, a 6-week assessment immediately following the treatment program, and a final assessment 6 weeks posttreatment (3 months postbaseline).

The control condition will be TAU. As these subjects will have access to any other online and offline drug counseling services that are available, they will be asked about their possible use of other treatment services over the course of observation at their final follow-up visit.

Follow-up assessments should be completed online after a reminder is sent by email, in which they also will be reminded that, upon completion of the entire 3-month follow up assessment, they will be compensated with 30 Euro (via either an Web-based voucher or the choice to make an online charitable donation). If the final assessment is not completed within 2 days, the same reminder will be sent out two more times, 2 days apart. If these reminders still go unanswered, participants will be contacted by phone within 1 week after the third email has been sent and offered an interview on the phone with study collaborators to complete the follow-up instruments. Should participants still refuse, they will be asked to answer questions about the primary outcomes only or—should they still refuse—to provide a reason for refusing, which will then be documented.

It is not uncommon for participants of Web-based interventions to take breaks, yet still complete the intervention later. Therefore, there are no dropout criteria relating to inactivity. The only dropout criterion is active withdrawal from the study by the participant, in which case only the data already gathered will be analyzed.

Figure 1 shows a flow chart depicting the flow of subjects through the study.

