General anxiety disorder-7	X		X
Adult ADHD^b^ Self-Report Scale-version 1.1	X		X
Quantity of cannabis use	X	X	X
Frequency of cannabis use	X	X	X
Cannabis Use Disorder Identification Test-Revised	X	X	X
Severity of Dependence Scale	X	X	X
Fragebogen Substanzanamnese	X	X	X
Client Satisfaction Questionnaire-I		X	
Intervention adherence^c^		X	
WAI-TECH^d^		X	
Negative effects according to Rozental			X

^a^DSM-IV: Diagnostic and Statistical Manual of Mental Disorders, 4th edition.

^b^ADHD: attention deficit hyperactivity disorder.

^c^Continuous assessment during 6 weeks.

^d^WAI-TECH: Working Alliance Inventory adapted for Web-based interventions.

CANreduce also features a responsive design and can automatically adapt to small screen devices such as tablets and mobile phones. Users can register online by choosing a username and providing a valid email address. To complete the registration process, users will have to click on a verification link sent to the email address specified, which will allow them to create a personal password, while preventing anyone from registering without a valid email address.

All data will be stored on a Web space hosted by an external provider that meets the IT security outsourcing regulations (99/2) of the Swiss Federal Banking Commission. Employees of the Web host will need to identify themselves with biometric data to gain physical access to the infrastructure.

Data will be extracted from the running Web-based database via Drupal and PHPmyAdmin. The data will then be stored at the PI’s institution on local computers for further processing and local file servers for archiving.

Each subject’s email address and phone number will be deleted after their participation in the study is complete and thereby, not available for either current or future analysis.

The investigator affirms and upholds the principle of every participant's right to privacy and that all personnel involved in the study will comply with applicable privacy laws. No individual data will ever be published or presented at scientific meetings.

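### The protocol expects TAU participants to re-register, but its only stated safeguard covers the same day and the same IP address

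*Protocol article*

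**What the plan says.** All of this is in the protocol article; no SAP is shown.

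- **Randomization and Trial Flow, allocation.** Once baseline is complete, participants are "randomized by a computer algorithm in a 1:1:1 ratio into one of three parallel groups", and the assignment is stored automatically.
- **Same section, text below Tables 1 and 2.** The passage opens "As participants assigned to TAU will immediately become aware of this" and continues that "we expect that some might try to circumvent their assignment by registering another account". The stated response is that the person will be "assigned to the original group when they try to register again on the same day based upon his or her Internet protocol address". TAU participants are told that they will be "provided access to the Web-based self-help treatment after 3 months".
- **Registration and Consent Procedure.** Participants give an email address and "phone numbers (only to get in contact with if follow-up questionnaires are not filled out". Real names and postal addresses are not recorded.
- **Technical Specifications.** The email link is verified, "preventing anyone from registering without a valid email address". Each subject's "email address and phone number will be deleted after their participation in the study is complete".
- **Measurements, last paragraphs.** All participants are asked whether they used any treatment other than canreduce.ch during the 3 months.

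**The concern.** The protocol names a specific threat to its TAU comparison and then fixes a safeguard that is easy to pass without any intent to deceive. Waiting until the next day is enough, and so is changing from a home connection to mobile data. The motive is documented: TAU participants know their arm at once and face a 3-month wait.

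A person who gets through could appear twice, once in TAU and once in an active arm. Three things would follow:

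- The TAU record would carry some of the program's effect, which pulls hypotheses 2 and 3 (each active arm against TAU) towards no difference.
- Two records from one person would be treated as independent.
- The recruited total could overstate the number of people.

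Analysis by intention to treat keeps each record in its assigned arm. It does not recognise that two records are one person.

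**Working it through.** **1. What the stated rules do with a second registration**

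| Second attempt | Stated rule | Result if the text is followed |
|---|---|---|
| Same day, same IP | Return to original group | Covered |
| Same day, other IP | None | Falls to the general rule: randomised 1:1:1 after baseline |
| Later day, any IP | None | As above |

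The only other stated check at registration is a valid, verified email address, which a second address satisfies. The 3-month question would not reveal the switch, because it asks about treatments other than canreduce.ch. A TAU participant who used the program through a second account could truthfully answer no.

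**2. Chance of an active arm**

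Two of the three arms are active, so P(active after k retries) = 1 − (1/3)^k. This gives 2/3 for one retry, 8/9 for two and 26/27 for three.

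**3. The plan's own sample size**

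Inputs (Sample Size Calculation): d = 0.30, two-sided alpha 5%, power 80%. The two-sample t test needs 175.4 per arm, rounded up to 176. Power at 176 per arm is 0.801, and 3 × 176 = 528. The stated figures reproduce.

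**4. Illustration of dilution**

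Assumptions that are not in the documents:

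- A share s of the 176 TAU participants re-registers once outside the rule.
- Each who reaches an active arm obtains the full program effect in the TAU record.
- d = 0.30 applies to active versus TAU.

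Then the contaminated share is c = s × 2/3, the diluted effect is d = 0.30 × (1 − c), and power is from the t test with 176 per arm.

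| s (assumed) | TAU participants reaching the program (176 × c) | c | d | Power |
|---|---|---|---|---|
| 2% | 2.3 | 1.3% | 0.296 | 0.791 |
| 5% | 5.9 | 3.3% | 0.290 | 0.774 |
| 10% | 11.7 | 6.7% | 0.280 | 0.745 |
| 20% | 23.5 | 13.3% | 0.260 | 0.682 |

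If the same people retried until they reached an active arm (c = s), power would be 0.785, 0.760, 0.714 and 0.612. Neither set allows for the duplicate records themselves.

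**5. Shared IP address**

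If IP alone were the key, a different person registering the same day from the same address might be placed in the first person's arm. Assume that 2% to 10% of participants fall in such pairs, with an intraclass correlation of 0.05 to 0.5. The design effect is 1 + share × correlation, so it runs from 1 + 0.02 × 0.05 = 1.001 to 1 + 0.10 × 0.5 = 1.05. Power runs from 0.80 to 0.78, a small loss.

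**The case against.** The strongest reply is that this is a condensed article. It is silent on later-day attempts; it does not say that they are randomised afresh. Duplicate detection and the choice of record to analyse are often left to the full protocol or the SAP. The email address, unlike the phone number, is not restricted to follow-up contact, so it may already be compared with earlier accounts. A second registration also takes effort: another verified address and the whole baseline assessment again.

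Much of this stands, and it limits what can be claimed. Four stronger readings are tempting, and the documents do not support them.

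- **That the 528 will contain duplicates.** No section says how second accounts are counted. The text permits duplicates but does not establish them.
- **That different people on one IP are forced into one arm.** The rule is written about the same person returning, and the article does not say that IP is the only field compared. This is an inference that applies to one day only and has a small effect.
- **That the trial's power is really 68-77%.** The re-registration share has no basis in the documents. Full dilution is an upper bound for any given share, since the protocol itself expects low adherence. The d of 0.30 is defined in Sample Size Calculation for the unenhanced against the guidance-enhanced version, not for active against TAU.
- **That deleting contact data makes detection impossible.** Deletion follows the end of each subject's participation. A TAU participant's email and phone therefore exist throughout the 3-month wait, which is when the motive to re-register exists.

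The reply does not remove the main point. The protocol raises the threat itself and states one rule to meet it, and that rule is too narrow. That is a stated safeguard fixed badly, not a detail left for another document.

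**Conclusion.** The point holds in limited form. As written, the safeguard stops only a same-day attempt from the same IP address. Nothing else in the article prevents or reveals a later attempt, which under the allocation rule would have a 2 in 3 chance of an active arm. The comparisons exposed are hypotheses 2 and 3. The comparison between the two active arms is not the target of this behaviour, since those participants are not told which version they have and have no wait to escape.

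The size cannot be derived from the documents. Under the assumptions stated above (one retry, full dilution, d = 0.30 for active versus TAU), power falls from 80% to about 79% if 2% of TAU re-register and to about 68% if 20% do. At the low end the loss is negligible. The case for acting is that the behaviour is foreseen, the bias runs in a known direction, and prevention is cheap. The sponsor should change this; it does not undermine the design. If the full protocol already has wider duplicate checks, one sentence saying so would settle most of the point.

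**What to change.** 1. At registration, compare the email address and phone number with those of all participants whose contact data are still held. This covers every TAU participant's 3-month wait without keeping any identifier longer than now planned. Return a match to the original account and arm.
2. Use the IP address only as a flag for review, not to allocate.
3. State that only a person's first randomisation is analysed, in the arm first assigned, and that only this record counts toward 528.
4. Report the number of suspected duplicates and run a sensitivity analysis that excludes them.
5. At 3 months, ask TAU participants whether they used CANreduce through another account.

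**Cost.** This needs a small change to the registration script and one added follow-up question. The phone number gains a second use, which conflicts with its present restriction to follow-up contact. The participant information must therefore be amended, and an ethics notification may be needed. The check is not complete: someone who uses both a new email address and a new phone number would still be missed, and so the follow-up question and the sensitivity analysis are needed as well.
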